#### Missing values

All of the above analyses will be complete case analyses. If a significant effect of the intervention after adjustment for multiplicity is noted three sensitivity analyses will be carried out where increasing degree of bias will be artificially induced by replacing missing values by constructed ones reflecting the degree of scepticism of the observed effect as follows.

#### Worst case scenario

Missing values will be replaced by the most pessimistic value in the opposite group. For time spent e.g. missing values in the group where the best effect was found will be imputed by the maximum value found in the other group and missing values in that group will be imputed by the minimum value found in the first group.

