### Sample size calculation and statistical analysis

Based on data in a previous study [15], we assume that participants in the intervention group and in the control group on the average will use 25 and 40 repetitions, respectively, to reach 'expert level'. With alpha set at 0.05 and beta set at 0.80, the sample size adds up to 98 participants in the trial.

The data will be analyzed using SPSS (Chicago, IL) version 15.0 and the SAS version 9.1. Two sided significance tests will be used.

*Analysis of the first experiment, i.e. instructor feedback approach vs. an independent approach: *The distributions of each outcome measure will be compared between the intervention group and the control group using the general linear uni-variate model and the analyses repeated with the co-variate semester number and the two protocol specified co-factors (indicator of sex, and indicator of computer game experience) included. A post hoc analysis including sex, the intervention indicator(I) and the interaction between I and sex will be conducted to explore the role of the sex.

If the assumptions of the general linear model (normally distributed residuals and variance homogenecity of the groups compared) cannot be fulfilled using simple transformations of the data, the distributions of the intervention group and the control group will be compared using a non-parametric test (Mann-Whitney) as will the two distributions of the results of the questionnaire reflecting the students self-perception at the end of the trial.

To adjust the P values for multiplicity Holm's procedure will be used [16].

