#### Strong bias

Missing values will be imputed by most pessimistic value in the group to which it belongs.

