#### Mild bias

Missing values will be imputed by mean value found during the complete case analysis of the group to which the missing value did not belong.

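### The worst-case imputation uses only the opposite arm's extreme, so it can be less sceptical than the strong-bias imputation, and the promised order of the sensitivity analyses is not guaranteed

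*Protocol article*

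**What the plan says.** The section Missing values makes the primary analyses complete-case analyses. Sensitivity analyses follow only when the effect remains significant once multiple testing has been allowed for. In that event, the text announces, "three sensitivity analyses will be carried out where increasing degree of bias will be artificially induced". Three subsections define them.

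- The harshest by name is the worst case, where the general rule is: "Missing values will be replaced by the most pessimistic value in the opposite group". The worked example, given for time, fills a gap in the better arm with the other arm's largest observed value, and a gap in the other arm with the better arm's smallest.
- The middle scenario, called strong bias, stays within the participant's own arm: "Missing values will be imputed by most pessimistic value in the group to which it belongs".
- In the mildest scenario, each gap takes the complete-case mean of the other arm.

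The names imply the order mild, then strong, then worst. The document contains no check of that order and no extreme taken over both arms together.

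**The concern.** The two harsher scenarios draw on different arms: the worst case on the opposite arm, strong bias on the participant's own arm. Neither extreme has to lie beyond the other. One very slow learner in the feedback arm is enough to make that arm's own maximum larger than the control maximum, and a significant mean difference does not exclude this. The scenario labelled worst is then not the worst, even within the values observed in the trial.

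What is at stake is how the three results are read. A graded scale lets a reader conclude that an effect which survives the worst case has also survived everything milder. Under the rules as written that inference is not valid.

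**Working it through.** **Rules side by side.** Let A be the arm with the better result and B the other. For repetitions and time, lower is better.

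| Missing in | Mild | Strong | Worst, as written | Worst, pooled |
|---|---|---|---|---|
| A | mean(B) | max(A) | max(B) | max(A and B) |
| B | mean(A) | min(B) | min(A) | min(A and B) |

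Strong bias is read here as against the effect, in line with the worst-case example. For a missing value in A, the worst case is milder than strong bias exactly when max(A) > max(B). For a missing value in B, it is milder exactly when min(B) < min(A). If strong bias instead means the poorest result in both arms, the reversal for missing values in A remains.

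**Numerical example (illustrates the algebra only).** A = 10, 15, 20, 25, 30, 35, 40, 45, 90 (sum 310, mean 34.44). B = 25, 30, 35, 40, 45, 50, 55, 60, 70 (sum 410, mean 45.56). The complete-case difference B − A is 11.11.

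Two further participants missing in A only:
- strong: 45.56 − (310 + 2×90)/11 = 45.56 − 44.55 = 1.01
- worst, as written: 45.56 − (310 + 2×70)/11 = 45.56 − 40.91 = 4.65

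Two missing in each arm:
- mild: (410 + 2×34.44)/11 − (310 + 2×45.56)/11 = 7.07
- strong: (410 + 2×25)/11 − 44.55 = 41.82 − 44.55 = −2.73
- worst, as written: (410 + 2×10)/11 − 40.91 = 39.09 − 40.91 = −1.82
- worst, pooled: 39.09 − 44.55 = −5.45

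In both cases the worst case as written is milder than strong bias. The pooled version is the most sceptical of the four.

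**Inputs for the frequencies.** The sample-size section gives means of 25 and 40 repetitions, two-sided alpha 0.05, 0.80 (labelled beta, read here as power) and 98 participants. It gives no standard deviation. Assuming 49 per arm, the SD that returns 98 is 15 / [(1.95996 + 0.84162) × √(2/49)] = 15/0.566 = 26.5. The simulations used lognormal and gamma counts with SDs of about 26 in both arms, or 20 (feedback) and 31 (control), and 2 or 5 participants missing in the feedback arm or in both arms. They kept only trials significant in favour of feedback at an unadjusted 0.05, with no Holm step.

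| Among significant trials | Raw t-test | Log-scale t-test | Mann-Whitney |
|---|---|---|---|
| Worst milder than strong | about 3-36% | 0-44% (log and rank together) | (see left) |
| Worst significant, strong not: largest value | about 6% | about 5% | about 0.5% |

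The detail behind the table:
- **Raw scale, SD about 26, 2 missing in the feedback arm only:** discordance 5-6%. With 2 missing per arm it is about 3%. With 5 per arm it is 0.5% or less, because almost nothing survives either scenario.
- **Log scale:** under 1% with 2 missing in the feedback arm; 2-5% with 5 missing in the feedback arm only at SD 26; 0-0.44% with losses in both arms at SD 26.
- **SD 20/31, raw scale:** order reversals fall to about 5-10% in most scenarios.
- **Mild against strong:** mild was the more sceptical of the two in at most 0.1% of simulated trials, so the weak point is the upper step.

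**The case against.** The algebra is not in dispute; the practical weight is. Four arguments deserve a hearing.

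1. **The analysis used for the raw figures.** The statistical section moves to transformation, and then to Mann-Whitney, if residuals are not normal or variances are unequal. For counts this skewed, raw-scale normality would almost always be rejected, so the raw t-test is not the branch the plan would follow. This stands. In a rank test, replacing a larger feedback maximum by the control maximum moves U by only half a unit per tied control value for each missing person. The order may reverse while the test hardly changes. The log scale still leaves 2-5% discordance in one setting, so the effect does not vanish.

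2. **The equal-SD assumption.** An SD of 26 in both arms gives coefficients of variation of 26/25 = 1.04 and 26/40 = 0.65, which favours a large feedback maximum. This also stands: the higher raw-scale reversal rates are the unfavourable end of the range.

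3. **Visibility.** A reader might infer that the trial would overstate its robustness by claiming to survive the worst case while failing a milder test. The document does not support that. It commits to all three analyses, so a reversal would be on view, and harm would need selective reporting that nobody proposes.

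4. **Severity of the existing rule.** Opposite-arm imputation is already harsh. On the raw scale with about 4% loss in the feedback arm only, significance survives in just 54-56% of significant trials. Pooled extremes lower this to 49-51%. The change is a refinement, but it is what makes the label true.

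**Conclusion.** The point holds as a defect of definition. The worst case as written need not be at least as sceptical as strong bias, so the promised order is not secured. This follows from the protocol's own rules and needs no distributional assumption.

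The frequencies are illustrative. They rest on assumed SDs, shapes, equal allocation and amounts of loss, and they leave out the Holm adjustment. Reversals of order can be common, but they seldom change the significance conclusion under the analyses the plan would use on skewed data. It would be wrong to read the reversal rate as the rate of misleading conclusions, or to say that the worst case is usually the milder scenario. The matter is minor and worth a wording change.

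**What to change.** In the worst-case subsection, define the replacement values over both arms and for every outcome:

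- Missing values in the arm with the better result take the most unfavourable value observed in either arm.
- Missing values in the other arm take the most favourable value observed in either arm.

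For repetitions and time these are the pooled maximum and the pooled minimum. For the weighted total score, which the statistical section analyses under the same rules, state the direction in which the score is read and apply the rule accordingly.

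Since max(A and B) ≥ max(A) and min(A and B) ≤ min(B), the imputed difference is then at least as sceptical as under strong bias in every data set. The same inequalities hold against the means used for mild bias. It would help to say explicitly that pessimistic in the strong-bias rule means against the observed effect.

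The change needs no new data and no extra analysis. The only cost is a somewhat less favourable worst-case result: about 5 percentage points lower survival in the raw-scale setting with 4% loss in the feedback arm (54-56% to 49-51%).

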#### Strong bias

Missing values will be imputed by most pessimistic value in the group to which it belongs.

#### Mild bias

Missing values will be imputed by mean value found during the complete case analysis of the group to which the missing value did not belong.

#### Analysis of the second experiment, i.e. the retention of skills

To analyze the data collected during the second experiment comprising time spent and number of repetitions used to reach the expert level by those persons who completed the first experiment the mixed model with repeated measures will be used. An unstructured co-variance matrix will be used. If convergence fails, a choice will be made between the compound symmetric (cs) and the cs plus a random intercept using Akaike's criterion. The basic model will be as follows:

Y=a+bI+ct+dtI

Where I is the indicator of intervention, t is time (time1 and time2 corresponding to experiments 1 and 2 respectively) and a through d are coefficients of the regression equation.

A significant main effect of time indicates that in general retention is present and a significant interaction between I and t indicates that the magnitude of the retention depends on the intervention. The analysis will be repeated with the semester # and the protocol specified stratification variables included as co-variates.

If a significant result is obtained it will be tested in a post hoc analysis if the retention depended on the students' sex or computer game experience (one factor at a time will be included in the model and the possible interactions involving the intervention and time analyzed).

*Missing values *Using the mixed model with repeated measures secures that all observed values are used and that no bias will be present as long as values are missing at random.

To examine the potential effect of bias resulting from values missing not at random a worst case but still not completely implausible scenario is defined as one where each value missing in the second experiment is identical with the corresponding value obtained during the first experiment. The missing values will be imputed accordingly and the analysis then repeated.

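### The fallback covariance rule for the retention analysis chooses between two identical models and always imposes equal variances, so the plan's no-bias statement does not cover it

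*Protocol article*

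**What the plan says.** The section on the second experiment (retention of skills) in the protocol article describes a repeated-measures mixed model with intervention I, time t and their product. There are two occasions: "t is time (time1 and time2 corresponding to experiments 1 and 2 respectively". The planned covariance is clear: "An unstructured co-variance matrix will be used". The fallback applies only after non-convergence: "a choice will be made between the compound symmetric (cs) and the cs plus a random intercept using Akaike's criterion".

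The interaction coefficient d carries the retention question: "a significant interaction between I and t indicates that the magnitude of the retention depends on the intervention". The data come from people who finished the first experiment ("by those persons who completed the first experiment the mixed model with repeated measures will be used"), so only the second value can be missing. On missing data the section states, without limiting it to one covariance structure, that "no bias will be present as long as values are missing at random".

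**The concern.** The fallback looks like a data-driven choice between two structures, but both candidates are the same marginal model. With two occasions, an unstructured matrix has three parameters (two variances and a covariance) and compound symmetry has two (one variance and a covariance). What the fallback gives up is therefore exactly the freedom for the variances to differ.

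Unequal variances are plausible here. The first experiment is novice learning, planned at 25 and 40 repetitions on average, and the second is relearning. The plan's worst case sets a missing second value equal to the first, which implies that second values are expected to be better. Fewer repetitions would normally spread less, but the article gives no SDs.

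Likelihood inference under missing at random needs a correctly specified covariance. If compound symmetry is imposed on unequal variances, the tests of time and interaction can be affected while the plan tells readers that no bias is present.

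**Working it through.** **1. The two candidates are identical.** Compound symmetry is V = s²·Identity + k·Ones. A random intercept with variance w adds w·Ones, giving V = s²·Identity + (k+w)·Ones. This is the same family, with k and w not separately estimable. REML fits to three simulated data sets gave the same -2 log-likelihood for both candidates: 1327.02, 1163.69 and 1194.10. In the first, Akaike's criterion was 1331.02 against 1333.02 when the redundant variance is counted. It ties when that variance is not counted. It can never favour the second candidate.

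**2. Inputs.** The article gives no figure for the retention model, so there is none to reproduce. From the sample size section: "the sample size adds up to 98 participants in the trial", hence 49 per arm, and first-experiment means of 40 (control) and 25 (feedback). The article states no SD. Reading the stated beta of 0.80 as power, n per arm = 2(1.960 + 0.842)²·SD²/15². With SD = 26.5 this is 2 × 7.849 × 702.25/225 = 49, so 98 in total. SD1 = 26.5 is thus a back-solved value.

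Assumptions not in the article: SD2 of 26.5, 13 or 8; correlation 0.5; second means 15 and 10; about 30% of second values missing. The true interaction is then (10 - 25) - (15 - 40) = 10.

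**3. Complete data.** In an example with unequal variances, both structures gave an interaction of 15.77 with SE 4.59. Nothing changes.

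**4. Why bias arises with missing values.** In each arm the model predicts missing second values from first values with some slope.
- The true slope is correlation × SD2/SD1. For SD2 = 8 it is 0.5 × 8/26.5 = 0.151.
- Compound symmetry uses covariance/average variance: 106/[(702.25 + 64)/2] = 106/383.1 = 0.277.
- For SD2 = 13 the slopes are 0.245 and 172.25/435.6 = 0.395.
- With equal SDs both are 0.5.

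As a first approximation, the bias in an arm's second mean is the slope error (0.126 or 0.150) times the gap between the mean first result of everyone in the arm and that of those observed again. If missingness is completely at random (MCAR), the gap averages zero. If the gap is the same in both arms, it cancels in the interaction but stays in the time effect. If the gap differs by arm, both are biased.

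**5. Simulation** (250 runs per row; 500 for SD2 = 26.5; simulation error of a bias about 0.3). CS is compound symmetry and UN is unstructured.

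| Missingness at time 2 | SD2 | CS interaction bias | CS model SE / empirical SD | CS time bias | UN interaction bias |
|---|---|---|---|---|---|
| MCAR | 26.5 | +0.32 | 0.99 | -0.27 | +0.33 |
| Opposite selection by arm | 26.5 | +0.22 | 0.99 | -0.01 | +0.17 |
| MCAR | 13 | -0.09 | 1.15 | +0.15 | -0.17 |
| MCAR | 8 | -0.09 | 1.16 | +0.12 | -0.13 |
| Same selection in both arms | 13 | +0.31 | 1.11 | +1.88 | +0.38 |
| Same selection in both arms | 8 | -0.06 | 1.16 | +2.19 | -0.08 |
| Selection in control only | 13 | -1.79 | 1.14 | +1.75 | -0.09 |
| Selection in control only | 8 | -1.36 | 1.11 | +1.63 | +0.40 |
| Opposite selection by arm | 13 | -3.59 | 1.00 | +1.87 | +0.44 |
| Opposite selection by arm | 8 | -3.81 | 1.07 | +1.81 | +0.32 |

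**6. Sensitivity.** Further runs used SD2 = 8, 10% missing in the feedback arm, and 30% missing in controls at the mean first result. The interaction bias was -0.8, -1.2 and -2.8 as the logit slope per SD rose from 0.5 to 1 to 2, and -0.5 with correlation 0.2 and slope 1.

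Selection can differ by arm without an arm-specific rule. One common rule on raw first-experiment repetitions selects more strongly in the arm with the higher mean. It gave -1.7 (SD2 = 13) and -2.7 (SD2 = 8), against -0.1 and -0.7 for unstructured on the same data (simulation error 0.3 to 0.4). A separate set of runs put the bias at about -1.1 to -1.4 for control-only selection or a common raw rule, the time bias at +1.4 to +4.5, and the SE excess at 6 to 22%.

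**The case against.** The strongest reply is that the fallback will hardly ever be used. The planned model has three covariance parameters and complete first values, and it converged in every completed simulation scenario. This stands and limits the importance of the point.

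Second, the redundancy itself does no harm: both candidates give the same estimate and standard error. This also stands. All the numerical effect comes from compound symmetry against unstructured.

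Third, the no-bias sentence can be read as describing the planned unstructured model, for which it is right if that model is correct. That is a fair reading, but the sentence follows the fallback in the same section and is not restricted.

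Fourth, the effect on inference is modest. With about 30% missing at random in both arms, SDs 26 and 8, and no true interaction, compound symmetry rejected in 2.9% of runs, against 5.3% for unstructured. With arm-specific selection it rejected in 2.8 to 7.9%, near 5% at moderate slopes.

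A reader might infer that the fallback biases the interaction whenever second values are missing, or under any missing-at-random pattern. Neither follows. With equal variances, with MCAR, or with the same selection in both arms, the interaction was unbiased within simulation error.

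**Conclusion.** The rule is wrong as written: it offers a choice that does not exist and can only end in equal variances. The consequence is conditional. If the fallback is used, second values are missing and the variances differ, the interaction's standard error is misstated, generally too large by about 5 to 20% under assumed SDs of 26 and 8 to 13, although one scenario showed no excess. If missingness also depends on the first result, the time effect is biased, by about +1.4 to +5 repetitions in the runs. If that selection differs between arms, the interaction is biased too, by about -0.5 to -4 repetitions against a true value of 10 in the main simulation. The larger values need steep or opposite selection.

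These sizes rest on an assumed second SD, correlation and dropout, and they apply to repetitions on the untransformed scale. The article supplies none of these quantities, and total time was not examined. The no-bias sentence does not hold for the fallback. This is a minor point that is worth correcting because it is cheap. It gives no reason to doubt the planned unstructured analysis.

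**What to change.** Delete the Akaike choice and name a fallback that keeps unequal variances. Either of these works:

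- Refit with other starting values in the heterogeneous-variance compound symmetry parameterisation, which for two occasions is the unstructured model.
- Because only the second value can be missing, fit the unstructured model without iteration through two ordinary regressions. With t coded 0 and 1: Y1 = m0 + m1·I, and Y2 = g0 + g1·I + g2·Y1 among those observed again. The interaction is then d = g1 + (g2 - 1)·m1.

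Limit the no-bias statement to the unstructured model. The cost is a sentence or two of plan text and slightly more analysis work. The two-regression route needs a delta-method or bootstrap standard error.

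### The retention rule reads the arm-by-time interaction as differential retention, but that interaction carries the primary effect with its sign reversed

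*Protocol article*

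**What the plan says.** The section on the second experiment analyses "time spent and number of repetitions used to reach the expert level by those persons who completed the first experiment". The model is Y = a + bI + ct + dtI, where I indicates the intervention and "t is time (time1 and time2 corresponding to experiments 1 and 2 respectively". No transformation or savings ratio is named for this experiment.

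Two reading rules follow. On time: "A significant main effect of time indicates that in general retention is present". On the interaction: "a significant interaction between I and t indicates that the magnitude of the retention depends on the intervention". The sensitivity analysis for missing data takes as its worst case that "each value missing in the second experiment is identical with the corresponding value obtained during the first experiment". This confirms that retention is scored as the change from time 1.

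The time-1 value is the primary outcome. The sample size section assumes that the intervention and control groups "on the average will use 25 and 40 repetitions, respectively". The section on the simulator task has every participant train until the same predefined proficiency level is met.

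**The concern.** Both arms leave experiment 1 at the same criterion. The planned gap of 15 repetitions at time 1 is therefore a difference in speed of acquisition, not in the skill available to be kept. A change score that starts from time 1 brings that gap into the retention comparison. The better feedback works in experiment 1, the further the interaction moves from zero when the arms are equal at six months.

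At stake is the between-arm conclusion of the second experiment: the written rule can announce differential retention where six-month performance shows none.

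The rule for the time effect has two looser ends. It gives no direction, so an increase would also count as retention. And with the tI term in the model and 0/1 coding of I, c is the change in the control arm alone, not a change in general.

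**Working it through.** **Inputs from the protocol article.** Time-1 means 25 (feedback) and 40 (control); two-sided alpha 0.05; a figure of 0.80 labelled beta, taken here as power; N = 98; the model and reading rules above.

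**Inputs assumed.** 1:1 allocation (49 per arm), and the time-2 mean, time-2 SD, within-person correlation and number retested. The document gives none of these, so ranges are shown.

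**Planned sample size.** The text reads "With alpha set at 0.05 and beta set at 0.80, the sample size adds up to 98 participants in the trial". No SD is given, so 98 cannot be reproduced independently. Solving back:

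SD = 15 / [(1.960 + 0.842) × √(2/49)] = 26.5

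With SD 26.5 the two-sample formula returns 49 per arm, or 98.

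**The interaction when six-month means are equal.** Let both arms need m repetitions at time 2:

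d = (m − 25) − (m − 40) = +15, for any m.

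This is exact and needs no outside figure. For example, with m = 8 the changes are −17 (feedback) and −32 (control).

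**How often it is significant (analytic).** With two time points, the interaction test is a two-sample test on within-person change:

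SD_change = √(s1² + s2² − 2ρ·s1·s2)

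With s1 = 26.5, s2 = 13.25 and ρ = 0.3, SD_change = √(702.25 + 175.56 − 210.68) = 25.8. The standard error is 25.8 × √(2/49) = 5.2, and 15/5.2 = 2.9, so power is about 82%. The ranges below are for ρ from 0 to 0.5.

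| Setting | Probability of a significant interaction |
|---|---|
| 49 per arm, s2 = 0.25·s1 | 78–88% |
| 49 per arm, s2 = 0.5·s1 | 71–90% |
| 49 per arm, s2 = s1 | 51–80% |
| 39 per arm, s2 ≤ 0.5·s1 | 61–82% |
| 25 per arm, s2 ≤ 0.5·s1 | 43–64% |
| 49 per arm, s2 ≤ 0.5·s1, alpha 0.025 | 60–84% |

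The last row is the first Holm step if the procedure is applied to the two retention outcomes.

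**Simulation with right-skewed (gamma) repetitions.** Equal time-2 means of 8 or 12, time-2 CV 0.5, correlation 0 to 0.6:

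| Retested per arm | Interaction significant |
|---|---|
| 49 | about 77–89% |
| 40 | about 67–80% |
| 30 | about 55–68% |

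The raw-scale interaction was never significant in the opposite direction. A direct comparison of the arms at time 2 was significant in about 5% of the same trials.

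**Equal proportional savings.** If both arms halve their count (40 to 20, 25 to 12.5), d = −12.5 − (−20) = +7.5. At 49 per arm this is significant in about 19–37% of trials for correlations 0 to 0.6, and clearly more often only as the correlation nears 1. In this case the feedback arm is better at six months (12.5 against 20), yet d has the sign of a smaller drop with feedback.

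**Log scale.** With equal time-2 performance, the log-scale interaction is still significant in about 37–85% of trials across these settings, because the time-1 difference remains in it.

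**The case against.** The strongest reply is that the plan measures retention as repetitions saved relative to original learning. Its worst case for missing data fits that reading, and for that quantity the interaction is the matching contrast. This stands as a matter of definition. It does not rescue the conclusion drawn, because a difference in savings still contains the primary effect with its sign reversed and does not measure skill kept from a common expert level.

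Four further limits stand.

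- **Direction.** A reader might infer that the plan would declare feedback harmful to retention. The rule states no direction and says nothing of harm. The smaller drop with feedback follows from the algebra together with the plan's reading of change as retention.
- **Frequency.** A reader might infer that a false signal is near certain, or that equal proportional savings would usually trigger it too. The first rests on an implied SD and assumed time-2 inputs. The second needs near-perfect within-person correlation.
- **Coding.** That c refers to controls only holds under 0/1 coding. The text calls I an indicator without giving values, and a factor-coded test of the main effect of time would average over the arms.
- **Importance.** Retention is introduced as an additional aim and is not listed under outcome measures. The primary comparison, its sample size and the data collection are unaffected.

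**Conclusion.** The point holds and should be fixed; it does not threaten the trial's main result. The section fixes both the model and its reading, so this is not a detail left to a later plan. With equal six-month means and the planned time-1 means, d = +15 exactly, and a significant result would be read as retention depending on the intervention.

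The chance of that is about 77–89% at full follow-up, 67–80% with 40 per arm and 55–68% with 30. These figures rest on the SD of 26.5 implied by N = 98, 1:1 allocation, a time-2 CV of 0.5 and correlations of 0 to 0.6. If the time-2 spread equals the time-1 spread with no correlation, the figure is about 51% even at full follow-up; with about half lost it can fall below 50%.

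**What to change.** - Make the between-arm contrast at time 2 the retention comparison (b + d with t coded 0/1), with its confidence interval and the planned covariates (semester, sex, gaming experience).
- If the interaction is kept, label it as a difference in repetitions or time saved relative to original learning, on the log scale if proportional savings are meant. State that it is not evidence of differential retention, and that the log scale does not remove its dependence on the time-1 effect.
- State that the overall time effect is averaged over the arms (c + d/2 under 0/1 coding) and counts as retention only if it is a decrease.

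The cost is a few sentences before the second experiment is analysed. The model and data are unchanged, and the fitted model already yields the time-2 contrast.
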